#### Enrollment and Data Collection

At the beginning of the study, all participating investigators will have a briefing session about the aims of the study and the enrollment process and instructions. During the control period, the participants will receive a quick daily questionnaire to calculate the number of eligible patients seen in consultation and the number of patients to whom a screening test is offered and accepted (see Multimedia Appendix 1).

#### Statistical Analysis

We will use a mixed effects approach that allows computing effects with step wedge [69]. Mixed models will allow us to evaluate effects of treatment and covariates in one model.

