### Evaluation of the Efficacy

#### Justification of Analysis

The study design for evaluating the tool will be a stepped wedge, randomized controlled trial. In this design, an intervention is launched sequentially to clusters over a number of time periods. This design is characterized by the fact that clusters are randomized for the time at which the cluster will switch from the control condition to the intervention condition. Stepped wedge designs incorporate data collection at each point (step) where a new group receives the intervention [46]. The period with no intervention is used as the control, which allows the study to take into account independent variables that might affect screening rate (such as migration changes or behavior changes brought on by the COVID-19 pandemic). This pragmatic design enables evaluations of how interventions would work in a real-world setting with limited exclusion criteria [64]. The other reason for choosing a stepped wedge cluster is ethics; it could be unethical or politically controversial to withhold an intervention that is deemed more effective than harmful to a control cluster [47]. The stepped wedge methodology is often used in public health research projects, especially in the field of HIV [47].

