#### Setting

The study will be carried out in 16 centers taking care of and treating migrants, including the provision of screening tests: immigration centers (OFII), hospital consultations specialized for underserved persons (PASS), nonprofit organizations offering rapid tests to migrants (not exclusively), ambulatory health care professionals (general practitioners, gynecologists, midwives) with large migrant patient populations. Different regions of France will be represented.

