#### Sample Size

The overall rate of screening currently carried out as part of the STRADA study in OFII centers is around 45% (average of 2 years, taking into account health professionals not offering a test and migrants refusing when the screening is offered). The primary hypothesis of this study is that the addition of the electronic screening app will increase this rate by 10%, from 45% to 55% (including an increase in the rate of screening offered by health professionals and a decrease in the refusal rate among migrants to whom screening is offered). With an alpha risk of 0.05 and a beta risk of 0.20, the total number of subjects required is 778 (ie, a workforce of 900 participants to be included to take account for missing data). Statistical comparisons will be made at the threshold of *P*<.05.

A moderate improvement was chosen because it would be a realistic but meaningful improvement, whereas a small effect size would be too small for clinical significance. Thus, our sample size will allow for the detection of moderate improvements, with ample data for subgroup analyses as well.

We will do a simple and pragmatic step wedge with 2 groups and 3 steps: first step without intervention, second starting intervention for 1 group (half of the centers), and third all centers with the intervention [65,66]. We plan to have 2 clusters with 450 participants in the OFII centers and 450 participants in the other structures (PASS, associated structures). Power and sensibility fit sample size and step wedge configuration were checked with the design effect method [67,68].

Subgroup analyses will be performed based on several variables (screening structure, level of health literacy, geographic origin of migrant, level of education, gender, age group) without adjusting the significance threshold.

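### The no-intervention period can absorb migration and COVID-19 change only through a step effect the protocol does not name; with that effect included, 778 or 900 participants fall well short of 80% power

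*Protocol article*

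**What the plan says.** Under Justification of Analysis, the protocol article explains how the design deals with outside influences on screening: "The period with no intervention is used as the control, which allows the study to take into account independent variables that might affect screening rate". The examples it gives are "such as migration changes or behavior changes brought on by the COVID-19 pandemic".

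Under Sample Size, the layout is fixed: "We will do a simple and pragmatic step wedge with 2 groups and 3 steps", namely "first step without intervention, second starting intervention for 1 group (half of the centers), and third all centers with the intervention". The Setting section gives 16 centres.

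The Statistical Analysis section has two sentences. The first commits to a mixed effects approach suited to a stepped wedge and cites a reference. The second reads "Mixed models will allow us to evaluate effects of treatment and covariates in one model". No section names a step, period or calendar-time effect.

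The Sample Size section requires 778 participants (900 enrolled, to allow for missing data) for a rise from 45% to 55% with alpha 0.05 and beta 0.20. It adds that the stepped wedge configuration was checked with a design effect method, but gives no ICC and no design effect.

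**The concern.** A control period does not by itself separate the effect of the app from the effect of time. In this layout, two thirds of the data (steps 1 and 3) come from steps in which every centre is in the same condition. Only step 2 has control and app centres side by side. A change in screening that runs across all centres is therefore partly aligned with exposure, and only a step effect in the model takes it out.

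The plan itself expects such change, so two things are at stake. If step is not in the model, the app effect carries part of the drift: upward drift looks like benefit and downward drift hides it. If step is in the model, the comparison relies much more on step 2, and the sample size has to be judged on that basis.

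**Working it through.** **Inputs from the protocol article.** Rates 45% and 55%; alpha 0.05 (sidedness not stated; two-sided reproduces the figure); power 80%; 778 required and 900 enrolled; 16 centres, half of them switching at each of two steps; share of centres on the app 0, 1/2 and 1 in steps 1, 2 and 3.

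**Assumptions, because the document gives no value.** Equal numbers in each centre-step cell, total variance 0.25, random centre intercept, ICC from 0 to 0.10, drift linear and common to all centres.

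**1. The plan's own figure.** For two independent proportions with unpooled variance, n per arm = (1.96 + 0.8416)² × (0.45×0.55 + 0.55×0.45) / 0.10² = 7.849 × 0.495 / 0.01 = 388.5, so 389 per arm and 778 in total. This is exactly the stated number. It is the size for individual randomisation, with no stepped wedge inflation.

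**2. How exposure is tied to time.** Mean step of control data: (1+1+2)/3 = 1.33. Mean step of app data: (2+3+3)/3 = 2.67.

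**3. Bias if step is omitted, for a drift of g points per step.**
- ICC 0: the estimate is the raw difference, so the bias is (2.67 − 1.33)g = 1.33g.
- Purely within-centre comparison (the upper limit): centred exposure is (−2/3, 1/3, 1/3) in early centres and (−1/3, −1/3, 2/3) in late centres, and centred time is (−1, 0, 1). The slope is (1+1)/(6/9+6/9) = 1.5, so the bias is 1.5g.
- Generalised least squares at N = 900 lies between these: 1.45g at ICC 0.05 and about 1.47g at ICC 0.10.
- At an assumed g = 3 points, the bias is 4.0 to 4.4 points against a target of 10. With SE = √(1/900) = 0.0333 at ICC 0, the standardised bias is 0.04/0.0333 = 1.2, and the chance of P<.05 with no app effect is 22.4%. At ICC 0.10 it is 26.5%.
- With step as a fixed effect, the bias from common drift is 0.

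**4. Power if step is included.** For I = 16 centres and T = 3 steps, the Hussey-Hughes variance is

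Var = I·s²(s² + T·τ²) / [(I·U − W)s² + (U² + I·T·U − T·W − I·V)τ²],

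where s² = (1 − ICC)×0.25/m, τ² = ICC×0.25 and m = N/48. Here U = 8×2 + 8×1 = 24, W = 0 + 8² + 16² = 320 and V = 8×4 + 8×1 = 40. So I·U − W = 64, and the second bracket is 576 + 1152 − 960 − 640 = 128.

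- N = 778, ICC 0: Var = s²/4 = 3/778, SE 0.0621; power = Φ(0.10/0.0621 − 1.96) = 36%.
- N = 778, ICC 0.10: s² = 0.01388, τ² = 0.025, SE 0.0695; power 30%.
- N = 900, ICC 0: SE 0.0577; power 41%.
- N = 900, ICC 0.10: SE 0.0649; power 34%.

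| N | Power without step | Power with step |
|---|---|---|
| 778 | 78-80% | 30-36% |
| 900 | 84-85% | 34-41% |

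The table covers ICC 0 to 0.10. Over that range, adding step multiplies the variance by 3.0 to 3.8. Variation between centres in their step effects would add to the variance and lower power further.

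**The case against.** The strongest counter-argument is that the protocol never says step is left out. The first sentence of the Statistical Analysis section commits to a mixed model method for stepped wedge designs and cites a source that is not at hand. The second sentence says what mixed models make possible and is not a closed list. The covariates are not itemised and could include step, and a condensed article commonly leaves model terms to the analysis plan. All of this stands. A reader might infer that the planned analysis omits time and will be biased, but that is an inference from silence.

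A reader might also take the exact match of 778 as proof that step will be omitted. It is not: the two-proportion formula contains no model terms, so it says nothing about which ones are planned.

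It can also be said that the no-intervention data include the half of the centres still on control in step 2, which is a concurrent randomised comparison, and that the justification describes a design choice and not an estimator. This is fair, but that comparison protects the estimate from drift only when the analysis separates the steps. As written, the credit goes to the control period.

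Finally, drift, ICC and equal cells are assumed. That limits the bias figures, which need a drift value. The power shortfall needs no drift: at ICC 0 it follows from the layout and the stated rates with equal cells. The design effect check does not answer it, because the required number is unchanged from the individually randomised size and no value is given.

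**Conclusion.** The point holds in conditional form. The justification credits the no-intervention period with something only a step effect can do in this layout, and the protocol does not name that effect. It is not established that the trial will give a biased estimate.

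The text needs correcting on either reading:
- **Step omitted:** the app effect shifts by about 1.3 to 1.5 points per point of common drift per step, up or down with the drift. At an assumed 3 points per step this is 4.0 to 4.4 points, with type I error about 22-27% at 900 participants.
- **Step included:** the stated 80% power is not delivered. It is about 30-36% at 778 and 34-41% at 900.

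These figures rest on 16 centres, equal cells, a random centre intercept and ICC 0 to 0.10. At ICC 0.20 the step-adjusted power is 32% and 36%, so the conclusion does not depend on the upper end of the range.

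**What to change.** - In Statistical Analysis, name the primary model: treatment and categorical step (three levels) as fixed effects, with a random centre effect. Centre-by-step and setting terms are optional.
- In Justification of Analysis, say that temporal change is handled by the step effect and the concurrent comparison in step 2, not by the control period alone.
- In Sample Size, restate the power of 778 and 900 under that model, and give the ICC assumed and the design effect obtained.

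The first two changes cost a sentence or two. The third costs more: the stated power becomes much less favourable, and the sample size may have to be reconsidered. That is better known before enrolment starts.

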#### Reporting the Results

The results will be published according to the validated reporting guidelines for stepped wedge randomized trials, which is the CONSORT (Consolidated Standards of Reporting Trials) guideline with the specialized extension [70]. A specialized CONSORT extension for the reporting of eHealth clinical trials has been created [71], which we will also use. We will present the 2 reporting guidelines as separate attachments.

#### Ethical Aspects and Possible Risks

The study will be submitted to the appropriate authorities: Comité de Protection des Personnes d’Ile de France (institutional review board) and Commission Nationale de l’Informatique et des Libertés (data protection agency). And the protocol will be registered in a clinical trials database [72].

As the study will be conducted among providers who are already experienced in conducting HIV and hepatitis B and C tests, the risks related to the testing and referral are minimal.

One potential risk is the introduction of a test to a population of patients who would not have been tested because of language barriers: patients not understanding the results of a test and having either a false sense of security or unjustified panic, receiving a positive result being distressed and the provider not able to comfort them because of language barriers, or receiving a positive result and not fully understanding the need for follow-up appointment.

To prevent and control these potential risks, we will only include centers that have sufficient resources to call for a phone interpretation service in case of a positive result or difficult communication.

Other risks specific to the use of an app to aid the communication around testing relate to confidentiality and data security. For example, there could be a lack of confidentiality if the audio version is played aloud and other people can hear from an adjacent room. It should be noted that this risk already exists for other consultations where health care professionals and migrants have a language barrier and use a phone interpreter service on a loudspeaker. There could also be a lack of data confidentiality if the sentences related to the results of the tests are recorded during the app session.

To prevent and control this risk, investigators conducting the study will be instructed to only use the app on a fixed computer or tablet securely kept (locked in a secure building) with a user password. During the development of the app, we will ensure that data security concerns are emphasized in the SRS. Sessions will be erased after a short period of time.

## Results

The study has received preliminary financing from the Agence Nationale de la Recherche contre le SIDA et les hépatites virales (French Agency for Research against AIDS and viral Hepatitis [ANRS]), followed by 1 year of funding from the Office Français de l’Immigration et Intégration (French agency for migration and integration [OFII]) and then by 3-year funding, including doctoral funding from ANRS. Further funding has been requested from private sponsors and Région Ile-de-France.

At the time of publication of this protocol, the initial qualitative study and systematic literature review have been completed. The study has been completed, and the results have been analyzed [48,49,73] for publication in a peer-reviewed journal. For the qualitative study, we interviewed 33 migrants undergoing a medical check-up at OFII. Migrants reported that difficult communication with a French doctor resulted in lack of confidence and lower compliance with treatment. Migrants with a French-speaking partner were either sidelined during the medical visits, being completely dependent on translation, or their partners helped them in learning new words needed for the medical visits. For migrants who preferred translation, the preference between physically present interpreters versus interpretation by phone or the use of applications was influenced by mainly 4 factors: perceived quality of translation (interviewees were divided, with some perceiving a human interpreter with knowledge of medical jargon most accurate and others trusting the application more), trust, intimacy, and empathy.

For the systematic review, we collected general information about the app, information about health literacy and cultural adaptation, information about the development of the app, evidence about the app’s acceptability and efficacy, and information about the use of apps. We included 61 articles presenting a total of 48 applications. About one-third of the applications (16/48) were designed solely to facilitate the interaction between migrants and a health care provider during a consultation, while the remaining two-thirds (32/48) were designed to promote health among migrants with a language barrier. Overall, the applications had good levels of acceptability, while only half had their efficacy evaluated. In those evaluations, the endpoints used are mostly related to reported behavior change and knowledge improvement, which is common for evaluations of health promotion programs.

Focus groups and Delphi consensus panel for selection of the tool’s content are currently underway.

## Discussion

### Implications of the Study

The project is well underway, with the qualitative study and systematic reviews completed. Their results will be used for the development of the app and the design of our study. The qualitative study has highlighted the necessity to have professional interpreters announce a positive result, preferably who can be reached easily. The qualitative study has also given us clues on how migrants use translation applications that can be useful for the development of our app: For example, the study found a strong desire to learn new medical terms; this possibility will be considered for the development of the app. Thanks to the systematic review, we have critically reviewed existing translation applications and noted the lessons learnt from their development and recommendations. We have compiled specific lists of features of such applications that are associated with an increased acceptability or efficacy. Those features will be suggested as options to include in our app in our Delphi survey.

If the study demonstrates an increase in screening rates and acceptability by migrants, further development may include international deployment, so as to make this app available for other countries and in other languages. Other developments might include expanding the health promotion features of the electronic tool, such as educational videos and a text messaging follow-up service for migrants who did not wish to undertake the screening immediately but were interested in a screening consultation in the future.

### Strengths and Limitations

The strength of this study is that it is conducted by a research team with multidisciplinary skills, including experience in developing patient-reported outcomes (including electronic patient-reported outcomes). The team has extensive experience with working with migrants within the STRADA study [74] and has worked with many professionals working in migrants’ health or HIV testing, all of whom are included in the steering committee, scientific committee, or associated committee. This study includes several methods (qualitative, quantitative, systematic literature review) and includes users in the development process.

The COVID-19 pandemic has disturbed the advancement of the study in many ways. The research team, specialized in public health and infectious diseases, has been developing research projects related to the pandemic, with a priority that has taken precedence over other existing research projects, including this study. This focus on COVID-19, as well as the postponement of recruiting new staff due to social distancing and remote working requirements and postponement of the focus groups for the same reasons, has delayed the advancement of the study. However, those short delays do not jeopardize the integrity and ultimately, the completion, of our study. In fact, better screening of infectious diseases is all the more necessary in the era of a pandemic.

### Conclusion

This study will develop an electronic screening app to aid migrants who speak little or no French and measure its acceptability and effectiveness in terms of public health. At the end of this project, this app will be able to be distributed to numerous health care workers, including nonprofessionals (such as volunteers), conducting screening with migrant audiences to be used in current practice. If proven effective, the electronic tool will make testing for HIV and hepatitis B and C among migrants more readily available and more widespread and will be an asset in the fight against infectious diseases.

## Appendix

Multimedia Appendix 1 Questionnaire for the control clusters.

Multimedia Appendix 2 Project peer-review report 1.

Multimedia Appendix 3 Project peer-review report 2.

Multimedia Appendix 4 Translation of the peer-review reports.

## Abbreviations

ANRS: Agence Nationale de la Recherche contre le SIDA et les hépatites virales (French Agency for Research against AIDS and viral Hepatitis)
CONSORT: Consolidated Standards of Reporting Trials
HBV: hepatitis B virus
HCV: hepatitis C virus
OFII: Office Français de l’Immigration et Intégration
PASS: Permanences d’accès aux soins de santé
PRISMA: Preferred Reporting Items for Systematic Reviews and Meta-Analyses
SRS: system requirement specifications
STRADA: Stratégie de dépistage de maladies infectieuses (Tuberculose, VIH, VHC, VHB) dans la population des migrants en France (Screening strategies for infectious diseases (Tuberculosis, HIV, Hepatitis C, Hepatitis B) in migrant population in France)
SUS: System Usability Scale
